Similarly, how best to communicate genetic research results to research participants remains unclear. Unlike patients with clinical genetic testing, research participants may not be prepared for actionable results, particularly if the results are unrelated to the reason they enrolled in research, or if they enrolled as healthy unselected participants many years prior (e.g. large biobanks). While having GCs disclose these results may be ideal to ensure understanding, minimize psychosocial distress, and optimize medical follow-up and cascade testing [43], GC workforce shortages and costs are barriers [43, 44]. Many programs have used GCs to share genetic research results [8, 35, 37, 45–47], while others have provide results to local health care providers [48, 49] who may lack the necessary expertise or resources, resulting in suboptimal patient outcomes [50]. Interactive patient-centered digital interventions and/or videos developed by genetic providers may provide a cost-effective alternative [51–54]. Further, these interventions could be paired with genetic counseling for participants with remaining questions, while still reducing overall provider time. Potential disadvantages include poor understanding, increased test-related short-term and/or long-term affective responses or suboptimal post-test behaviors (e.g. medical management and cascade testing). Limited data exist on patient outcomes, clinical outcomes, and costs associated with various approaches. Empirical data are needed to inform best approaches for pre-disclosure education and returning results to realize benefits for participants.

Although research participants have reported high interest in receiving research results [15, 48, 55–62], uptake has been lower when results have been offered (48–86%), particularly in biobank studies where return of results was not emphasized during enrollment and uptake has generally been around 50% [36, 38, 63–69]. There are limited patient-reported outcomes in research settings [63–65, 70], although some genomic implementation studies report no psychological harms with return of genetic findings [71, 72]. In the RESPECT2 study, research participants could choose pre-disclosure education with a GC or a patient-centered digital intervention. All participants received results with a GC. Favorable cognitive (e.g. knowledge) and affective (e.g. distress and uncertainty) responses were found, although the number of actionable results was small [73, 74]. 

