### Objectives

The goal of the RESPECT3 Study is to conduct a Hybrid Type 1 effectiveness-implementation study to evaluate digital delivery alternatives for pre-disclosure education and return of actionable genetic research results. Based on our preliminary data and related research, we include both digital pre-disclosure education interventions and a private web-based portal for return of individual research results as an alternative to result disclosure by a genetic provider. Additionally, the study incorporates three chatbots designed to increase completion of pre-disclosure education, receipt of results and clinical confirmation testing.

#### Specific aim 1

Our primary aim is to evaluate in a randomized study whether disclosure of actionable genetic results by a digital intervention (digital-ROR) provides non-inferior short-term and longitudinal outcomes (knowledge, psychological distress, health and psychosocial behaviors and costs) compared to remote telehealth disclosure by a genetic counselor (GC)(e.g. usual care).

#### Specific aim 2

Our secondary aims are to evaluate the uptake of supplemental digital education (offered through a digital intervention or a chatbot) among Penn Biobank research participants notified of the option to opt-out of receipt of actionable genetic research results (Aim 2a), to evaluate the frequency of opting-out of receipt of actionable genetic research results (Aim 2b) and to evaluate the impact of use of digital education on opting out of receipt of actionable results (Aim 2c).

#### Specific aim 3

Our third aim is to conduct a multi-stakeholder mixed-methods process evaluation to understand the potential moderators (e.g. intervention usage, sociodemographic factors, genetic test result) of short-term and longitudinal outcomes to understand who benefits more or less from digital education and digital return of results (Aim 3a), and to understand the facilitators and barriers to implementation of digital interventions for return of actionable genetic research results and recommendations for future adaptation and sustainability (Aim 3b).

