
#### Moderators of uptake and patient reported outcomes (aim 3a)

Moderators are collected at baseline and include sociodemographics, health literacy, comfort with technology and general health status. Sociodemographic data includes race/ethnicity, education, marital status, gender, age, zip code, health insurance status, usual source of care status, employment status, financial wellness [130] and household income. Test result, including cancer versus cardiovascular/other actionable result and the specific gene are recorded. General health status [129] and personal and family history of cancer and cardiovascular disease are included in the baseline survey. Health literacy is assessed at baseline (T0) with 3 items validated to detect inadequate health literacy in clinical medical populations [131]. Comfort with technology is assessed with selected items from the NCI Health Information National Trends Survey (HINTS), including internet and social media use electronic medical record use and perceptions of privacy (7 items) [132].

Additionally, individual use of digital interventions are recorded throughout the study to evaluate the impact of intervention usage (e.g. dosage) on outcomes and who benefit from supplemental digital education or digital-ROR.

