### Data analysis plan

#### Primary non-inferiority analyses

We hypothesize that disclosure of actionable results by digital-ROR, with access to a GC, can provide non-inferior short-term and longitudinal cognitive, affective, and behavioral outcomes, and lower costs. Primary effectiveness outcomes include: post-disclosure knowledge and cancer or cardio disease-specific distress. We will test whether the receipt of results differ between arms as a secondary analysis. Receipt of results is considered a health behavior. For the 2 primary analyses, we will apply non-inferiority tests to examine if access to digital-ROR is non-inferior to GC disclosure. We will conclude non-inferiority if the upper bound of the randomization effect 97.5% one-sided confidence interval [CI] for cross-sectional T1 responses do not cross a -0.45 standardized difference threshold (i.e., margin) for knowledge and a 0.2 standardized threshold (i.e., margin) for disease-specific distress in the direction that would suggest that digital-ROR is worse. A standardized difference is the difference after variables are scaled to have standard deviation (SD) one with respect to baseline SD. We based the margins on what might be considered clinically relevant effects given our pilot data. We will use intention-to-treat approaches, comparing randomized arms, with confirmation by per-protocol analyses (i.e. restricting sample to those who properly used the method of disclosure as assigned). We will only declare non-inferiority if both intention-to-treat and per-protocol analyses are consistent, as recommended [133, 134]. For the secondary outcome receipt of results, we will examine non-inferiority of proportions. We will declare non-inferiority if the upper bound of the randomization effect 95% one-sided confidence interval for receipt of results is < 10% in the direction that favors usual care. Since all participants will have the option to speak with a GC, we will conduct secondary as-treated analyses (i.e. based on whether genetic counseling was actually received in both arms).

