In secondary analyses, we will use T-tests and Fisher’s exact tests for superiority testing. We will assess balance of potential confounders (e.g. age, race, study site) between arms using T-tests or Fisher’s exact tests. We will use multiple linear regressions (continuous outcomes) and logistic regressions (presence of a behavior such as receipt of results or uptake of confirmation testing) to examine effects after adjusting for potential confounders inadequately balanced. For longitudinal analyses that include all three time points (T0, T1, and T2), we will estimate regressions by Generalized Estimating Equations (GEEs); we will include main and interaction terms between arm and time [135]. 

Intervention costs will be estimated for each study arm, and mean costs per participant will be reported. We will perform a benefit-cost analysis comparing the two study arms, where net benefit (or cost) of the intervention is estimated as the difference in mean downstream costs (i.e., savings in health care expenditures attributable to the intervention) minus the difference in mean intervention costs. In sensitivity analysis, we will vary both intervention cost items and the costs of downstream health care services over reasonable ranges and examine the impact on results. The time horizon of the benefit-cost analysis will be limited to the 12-month follow-period. We will not project longer-term outcomes, nor will we estimate the potential economic impact on family members of genetic test results in study participants, as these are beyond the scope of this study.

#### Sample size justification for aim 1

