#### Aim 3 analyses

We hypothesize that moderators will identify those who benefit more and less from the eHealth interventions and can inform policies for return of results. For moderation (i.e., effect modifiers), we will include in regressions described in Aim 1 an indicator variable for randomization arm, panel time indicators (for longitudinal models examining all three time points), the potential moderator variable, and all two-way and relevant three-way interactions among the arm/time/moderator variables [135]. To maintain power, we will examine non-time moderators separately.

Qualitative data will be analyzed using an iterative, deductive content analysis approach and CFIR as the coding framework [107, 110, 137]. The qualitative data will include: (a) participant surveys and key informant interviews; (b) notes and debriefing from our research team meetings. Guided by consensual qualitative methods [138, 139], two independent coders will review notes and assign responses to CFIR constructs. Using a convergent mixed-methods approach [140], we will merge quantitative and qualitative data, organized by the 5 CFIR domains to evaluate which constructs were associated with, or more prevalent among: (a) patients who used the digital interventions exclusively versus those who used digital interventions and requested a GC versus those who requested to speak with a GC and declined use of digital interventions, (b) participants who used chatbot options versus web-based options, (c) participants who had confirmation testing and clinical medical follow-up versus those who did not, and (d) those who shared results with multiple relatives versus those who did not, providing an opportunity to comprehensively evaluate facilitators and barriers to implementation of digital alternatives for return of actionable genetic research results in large biobanks and research cohorts. We will use descriptive statistics, correlations, and generalized linear models, assuming appropriate link and family functions, to examine quantitative variables associated with barriers and uptake. We will estimate longitudinal models by Generalized Estimating Equations.

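### Receipt of results is judged on an absolute difference, but its covariate-adjusted and moderator analyses are logistic: report them as risk differences too (minor, cheap improvement)

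*Protocol article*

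**What the plan says.** All references are to the protocol article.

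- **Scale of the receipt decision.** Under Primary non-inferiority analyses: "For the secondary outcome receipt of results, we will examine non-inferiority of proportions". The limit there is 10%. Under Sample size justification for aim 1 it is 11%, with 55% against 44% and 255 per arm. Both are absolute differences.
- **Adjusted analysis.** Also under Primary non-inferiority analyses, the secondary analyses adjust for poorly balanced covariates. Binary outcomes are handled by "logistic regressions (presence of a behavior such as receipt of results or uptake of confirmation testing".
- **Scope of Aim 3a.** The outcomes section is headed "Moderators of uptake and patient reported outcomes (aim 3a", so uptake is covered as well as the questionnaires. The objective is "to understand who benefits more or less from digital education and digital return of results (Aim 3a".
- **Moderation model.** Under Aim 3 analyses: "we will include in regressions described in Aim 1 an indicator variable for randomization arm", together with "all two-way and relevant three-way interactions among the arm/time/moderator variables".

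The Aim 3 text names no effect scale. The logistic scale for receipt and confirmation testing follows from its reference back to the Aim 1 regressions.

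**The concern.** One outcome, receipt of results, is handled on two scales. The verdict uses percentage points; the adjusted effect and the moderator effects come from a model whose coefficients are log odds ratios.

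This has two consequences. First, if the arms are imbalanced on a covariate, readers will want to know whether the receipt conclusion survives adjustment, and an odds ratio does not answer that in the units of the limit. Second, who benefits more or less from digital return of results is, for uptake, a question of how many more or fewer people in a group receive them. An interaction term in a logistic model tests whether odds ratios are equal, which is a different question once groups differ in uptake. The Aim 3 text expects the moderator findings to be useful for policy, so the scale on which they are stated matters.

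**Working it through.** **1. The plan's own figure.** Inputs from Sample size justification for aim 1: 255 per arm, 55% against 44%, one-sided 5%, pooled standard error.

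- Pooled rate = (0.55 + 0.44)/2 = 0.495; pooled SE = √(2 × 0.495 × 0.505/255) = 0.0443.
- Unpooled SE = √((0.55 × 0.45 + 0.44 × 0.56)/255) = 0.0440.
- Power = Φ((0.11 − 1.645 × 0.0443)/0.0440) = 80.1%.

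The stated power of more than 80% reproduces, and it belongs to an absolute limit of 11 points. With 10 points (55% against 45%) the same calculation gives about 73%.

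**2. Equal odds ratios, unequal differences.** Let p be uptake in the genetic counselor arm. Digital uptake = OR × p/(1 − p) ÷ [1 + OR × p/(1 − p)]. The odds ratios are assumed. The 48% and 86% are the ends of the range in Background ("uptake has been lower when results have been offered (48–86"). That range is between studies and is used here only as an assumed spread between subgroups.

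| Counselor-arm uptake | Loss at OR 0.60 | Loss at OR 0.65 |
|---|---|---|
| 48% | 12.4 points (to 35.6%) | 10.5 points (to 37.5%) |
| 55% | 12.7 | 10.7 |
| 70% | 11.7 | 9.7 |
| 86% | 7.3 (to 78.7%) | 6.0 (to 80.0%) |

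Within each column the logistic interaction is exactly zero. From 48% to 70% the losses differ by about 1 point; at 86% the gap is 4.5 to 5 points or more.

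**3. The reverse.** Take an equal loss of 8 points in both groups.

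- 48% to 40%: OR = (0.40/0.60)/(0.48/0.52) = 0.72.
- 86% to 78%: OR = (0.78/0.22)/(0.86/0.14) = 0.58.
- Ratio = 0.577/0.722 = 0.80.

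An identical absolute effect appears as an odds-ratio interaction.

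**4. The adjusted effect.** An adjusted odds ratio of 0.65 could stand for a loss of 10.7 points or 6.0 points, depending on uptake, so it cannot be placed against 10 or 11 points. It also differs in kind from the unadjusted odds ratio. In an even mix of the 48% and 86% groups with OR 0.60 in each, the counselor arm has (48 + 86)/2 = 67.0% and the digital arm (35.64 + 78.66)/2 = 57.15%. The overall OR is (0.5715/0.4285)/(0.670/0.330) = 0.66, not 0.60, without any confounding.

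**5. How often this would matter.** In that mix the overall loss is 67.0 − 57.15 = 9.85 points and the pooled SE with 255 per arm is 4.3 points. Non-inferiority for receipt is declared with probability Φ((limit − 9.85)/4.3 − 1.645), about 5% at 10 points and 8% at 11. With OR 0.65 the overall loss is 8.3 points and the probabilities are about 11% and 16%.

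**6. Power of the interaction tests.** Split 510 evenly into four cells of about 127.

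- Additive scale, OR 0.60: the contrast is 12.4 − 7.3 = 5.0 points after rounding, SE 7.8 points, two-sided 5% power about 10%.
- Odds-ratio scale, equal 8-point losses: log ratio 0.22, SE 0.42, significant about 8% of the time against a nominal 5%.

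**The case against.** The strongest reply is that a logistic model is not wrong, that risk differences can be derived from it afterwards, and that this is reporting detail a journal article leaves to an analysis plan that is not shown. Much of that stands. Nothing in the article says that only odds ratios will be reported or that a null interaction will be read as no moderation. The receipt decision itself is on the right scale.

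A reader might infer that the plan would conceal a subgroup failing non-inferiority. The documents do not support that, for four reasons.

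- The limit applies to one comparison, arm against arm for receipt. No subgroup margin is set, and confirmation testing has no limit at all.
- The 48% to 86% range is between studies. Background puts biobank uptake at around 50%, and the sample size uses 55% and 44%, where the two scales nearly agree.
- The example seldom coincides with a favourable overall result. If the observed loss is small enough to declare non-inferiority (about 2.7 to 3.7 points at rates near 50%), a common odds ratio implies at most about 4.8 to 6.4 points in any subgroup between 48% and 86% uptake that makes up at least 10% of the sample.
- With about 10% power, an additive interaction test would usually be null as well. Changing scale does not cure that.

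The two primary outcomes are continuous and use linear models, so they are unaffected.

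What the reply does not remove is that the article does fix the model family for the adjusted and moderator analyses and the scale of the limit, and the two do not match. Aim 3a also does not depend on a favourable overall verdict.

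**Conclusion.** The point holds as a minor one, worth making because the remedy is nearly free. The adjusted receipt effect, as an odds ratio, cannot be set against the trial's absolute limit; this needs no assumption about subgroups. For Aim 3a, an odds-ratio interaction does not show how many more or fewer people in a group receive results or complete confirmation testing.

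The size depends on assumptions the documents do not settle: subgroup uptake and the odds ratio. At an assumed common odds ratio of 0.60, the gap between groups at 48% and 86% uptake is about 5 points; for groups between 48% and 70% it is about 1 point. The link from Aim 3a to the logistic scale is by cross-reference, and Aim 3a is not a primary aim. The figures do not show that any subgroup would breach a margin, and the 10- or 11-point limit should not be used as a subgroup non-inferiority test.

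**What to change.** First reconcile the two limits for receipt, 10% under Primary non-inferiority analyses and 11% under Sample size justification for aim 1. Until then there is no single value to set an adjusted difference against.

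Then keep the logistic models and add wording to this effect:

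- The adjusted effect on receipt is reported as a standardised risk difference (predicted probabilities averaged over the sample under each arm), with a delta-method or bootstrap confidence interval, on the scale of the margin.
- For receipt and confirmation testing, Aim 3a reports risk differences by moderator level with confidence intervals, beside the odds-ratio interaction. These are descriptive estimates, not subgroup non-inferiority tests.
- Absence of moderation is not concluded from a null odds-ratio interaction alone.

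The cost is a few lines of analysis-plan text and a post-estimation step, with no new data and no change to sample size. The downside is that two scales are reported and may point in different directions, so the text should say in advance that statements about how many people receive results rest on the risk differences.

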## Methods

### Study design

The RESPECT3 Study is a Hybrid Type 1 effectiveness-implementation study, to evaluate digital alternatives for pre-disclosure education and return of actionable research results in a prospective randomized trial. The study includes a concurrent CFIR (Consolidated Framework for Implementation Research)-informed process evaluation to consider future implementation and sustainability of using eHealth interventions for return of actionable genetic research results in large and sociodemographically diverse research cohorts. We use a two-step process to notify biobank participants of the return of results process. In Step 1, participants with an actionable result and procedural controls (no actionable result) are invited to digital pre-disclosure education and provided options for opting out of results. In Step 2, those with actionable results who have not opted out are randomized to receive results via a digital disclosure intervention (digital-ROR) or with a GC (Fig. 1).

**Fig. 1 Fig1:**
[figure not shown]
Schema

### Ethics approval

The original PMBB consent stipulated that actionable results would be returned but did not describe the various types of results or when and how these would be returned. It also did not specify how one might decline (e.g. opt out of) results. Thus, the Return of Results (ROR) protocol is an extension of the original PMBB protocol and consent process. It is not “a new study” but rather is a process for implementing the obligation that was already established in the PMBB consent, when it was stated that results that could impact one’s health would be returned. Thus, the ROR process provides PMBB participants with current and comprehensive information on what results are being returned and how and the opportunity to decline these results if they desire. These activities (with the exception of the surveys) are all a direct extension of the obligation set in the original consent regarding results. We do require an informed consent for the surveys, but if a participant declines the surveys, we are still bound by the original PMBB consent to provide actionable results as previously stated. The participants will receive a $50 gift card for each survey completed.

### Digital pre-disclosure education and return of results intervention

Informed by prior research, we developed a mobile-ready, patient-centered multi-modality digital pre-disclosure education and return of results intervention (digital-ROR) as alternatives to genetic counseling to reduce participant burdens and steps to receiving actionable genetic research results. The study team adapted the digital education tool for this study from the stakeholder-informed RESPECT multi-modality pre-disclosure web education (e.g., digital) intervention and modified it based on user and usability testing with biobank participants. Digital-ROR was specifically developed for this study. Both digital interventions cover the same content as genetic counseling and were developed with patient feedback to meet the needs of a diverse clinical population. Informed by the tiered-binned model, the interventions include ‘‘indispensable’’ Tier 1 information presented to all participants, and ‘‘optional’’ Tier 2 information for varying needs. The digital pre-disclosure education intervention consists of six modules and nine optional videos (Table 1; Figs. 2a-b). The digital pre-disclosure education reviews in more detail the types of actionable results being returned, the differences between research and clinical testing, the need for confirmation testing and the benefits, risks and limitations of receiving actionable genetic research results and study steps and procedures. The digital-ROR intervention has four modules and three optional videos (Table 2; Fig. 3). It shares the actionable mutation identified, associated risks and general management approaches. It also emphasizes the need for clinical confirmation testing and medical follow-up. To help ensure access, the digital interventions are optimized for use by mobile devices and various web browsers and are accessible through an individual user ID and passcode. The digital-ROR intervention has an additional birth month and year field which serves as an added layer of privacy. To help ensure accuracy and quality, all actionable research results are entered into a case report form and uploaded for each randomized participant by a study staff member and a second study staff member confirms accuracy of the actionable genetic research result and uploaded research result in the study participant’s private web-portal. At least one of these staff members is a genetic counselor and these steps occur for each result uploaded into the private web-portal prior to the result being accessible by the study participant.
